### Randomization and blinding

After screening, interview, and evaluation of qualifications, the subjects who meet the inclusion criteria will be randomly divided into the breath regulation group, body regulation group, heart regulation group, and control group using a random number generator. The random list will be generated by an independent person using a computer to ensure the anonymity of the allocation.

The distribution order will be saved in sequential numbers in opaque and sealed-bound envelopes with aluminum foil inside to ensure that the envelopes are not visible in bright light. After the details of the subjects are written on the envelope, the envelope can be opened.

The lead investigator and data analyst will not participate in any intervention. The blind method will be used for the outcome assessor and data analyst to prevent the selective reporting of outcome variables. The subjects, coaches, researchers, and follow-up personnel will not be blinded, due to the particularity of sports intervention. The evaluators will not participate in the recruitment and distribution of subjects, and subjects, coaches, and researchers will be asked to refrain from discussing the intervention measures with the evaluators before the end of the experiment. In the event of serious side effects, blinding can be removed at the discretion of the outcome assessor.

### Interventions

In addition to health education, the subjects in the three intervention groups (“breath regulation group,” “body regulation group,” and “heart regulation group”) will perform the exercise intervention 5 times a week for 60 min (including a 10-min warm-up exercise, a 40-min stretching exercise, and a 10-min relaxation) for 6 months. The control group will not carry out any interventions except health education. All subjects will be asked to maintain their pre-intervention lifestyle and refrain from any strenuous exercise that may affect the test results. Air quality may be a factor in the effectiveness of the intervention [25]; therefore, the intervention groups will receive exercise intervention from 7:00 to 8:00 in the morning in different parks in Mengcheng County (different groups in different locations). Borg ratings of perceived exertion (RPE) (1982) [26] are a practical, simple, and cheap method to monitor internal load [27]. This scale has a high correlation with heart rate, exercise load, fat consumption, sugar consumption, and total energy output, and can be used as an effective index to judge load intensity [28]. All participants in the three intervention groups will wear a heart rate meter (polar s610i, Finland) to measure their heart rate during each exercise. Subjects will receive an education session on the RPE scale prior to the start of the intervention so that the RPE can be assessed at any time during the exercise intervention. Before the experiment, training courses will be conducted with the help of the staff, including coaches and result evaluators. All the coaches have more than 10 years of experience in TCHE and will undergo one-to-one training before the teaching sessions. The exercise contents of the three groups were selected from restored ancient health books approved by experts in fitness Qigong, traditional Chinese medicine, and related fields [29–32].

#### Breath regulation group

In the breath regulation group, the subjects will perform eight movements to practice breathing while moving to the tune of assigned music. The breathing modes, including natural breathing, nasal suction, mouth spitting, and abdominal and non-abdominal breathing, are simultaneously combined with limb movements, such as flexion and extension of the upper limbs, pulling of the upper limbs, and left and right rotation of the body. The combination of multiple breathing modes may improve respiratory muscle strength and endurance by reducing the relative proportion of the anatomic invalid space of the respiratory tract, enhancing the gas exchange between the alveoli and capillaries, and increasing the range of motion of the diaphragm [33]. Simultaneously, the upper limb movement increases the depth of breathing by stretching and massaging both sides of the body. This dredges the meridians and airways to improve breathing thereby improving lung function.

#### Body regulation group

The eight movements in the body regulation group are performed in a standing position. In contrast with the breathing combined with limb flexion and extension exercise in the breath regulation group, the subjects in the body regulation group need to pay more attention to the strength exercise of the lower limbs while flexing and extending the upper limbs, particularly in the semi-squat position, standing-to-squatting conversion, and one-leg support position. Through flexion and extension and the continuous change of the body’s center of gravity, the muscle tissue is contracted and stretched, dredging the meridians and collaterals. This enhances the strength of the quadriceps femoris and the balance of the body [20]. It is important to note that the strength of the quadriceps femoris is related to lung function [34]. Concurrently, upper limb movements include shoulder and chest expansion, which are conducive to breathing.

#### Heart regulation group

Heart regulation refers to the regulation of the spirit and consciousness, through the modulation of thinking [35]. The twelve movements of the heart regulation group are performed in the standing posture, according to Zhuangzi’s health fables. Each movement corresponds to a health fable. Health fables express the importance of health through metaphorical stories. Zhuangzi is an ancient Chinese figure representative of health preservation, and the term “health preservation” is first found in *Zhuangzi*. The fables regarding health and life philosophy, recorded in *Zhuangzi*, can be combined with body movements to allow better regulation of the spirit and consciousness.

Before practice, the coach explains the implication of each action. During the practice, through a combination of allegory and music, the subjects can keep calm, eliminate distractions, and relax. In mindfulness meditation, the mind focuses on breathing and related acupoints; in exercise meditation, the mind focuses on the coordination of body movement and breathing to guide the movements [36]. Thus, it can regulate the viscera, dredge Qi and blood, and improve lung function.

#### Control group

The control group will receive health education for the prevention and control of middle-aged and elderly chronic diseases without any exercise intervention. Concomitantly, the exercise time and physical labor during the intervention period will be recorded for each subject in the control group.

### Strategies to improve adherence to interventions

Subjects will not be able to change their group during the intervention. To better monitor the subject’s skill practice, all exercises will be conducted under the guidance of a coach in the designated venue until the end of the 6-month intervention. The coach will monitor the attendance before each exercise, and the researchers will conduct telephone follow-ups. In the first 1–2 weeks, the main task will be to learn the movements with the explanation and demonstration of the coaches. Between weeks 3 and 6, the main task will be to improve the standardization of the movements. The coaches will further correct the movements based on the subjects’ basic mastery of the movement structure and strengthen the interaction between different movements. Between weeks 7 and 24, the main task will be to practice repeatedly to increase the subject’s understanding of the action.

### Outcomes

The changes of pulmonary function from baseline to the end of the interventions will be assessed using the pulmonary function evaluation system (MasterScreen, Germany). The main outcome measure is forced vital capacity (FVC), and the secondary outcome measures are the forced expiratory volume in 1 s (FEV1), FEV1/FVC ratio, vital capacity (VC), and maximal voluntary ventilation (MVV). All results will be evaluated at baseline and 3 months and 6 months after the intervention by the same evaluator. The test will be conducted in a room with good ventilation and constant temperature and air pressure to minimize the influence of confounding variables on lung function [37].

The pulmonary function of the patients will be evaluated according to the standards of the American Thoracic Association/European Respiratory Association (ATS/ERS) [38]. Technicians will be required to skillfully grasp the correct operation of the inspection items and have a good service attitude. In the process of inspection, technicians will verbally and non-verbally encourage participants to complete the inspection. Before the test, the technician will explain the purpose and method of the lung measurement examination to the participants. In order for the participants to understand the task of completing maximal inhalation and exhalation, the technicians will demonstrate the proper technique. The height, weight, name, age, and other parameters of the subjects will be recorded. For the measurements of height and weight, subjects will be asked to be barefoot and use light clothes. The subjects will be standing, and the height of the instrument will be adjusted to maintain the head in a front-facing position. During the test, a mouthpiece will be wrapped tightly with the lips, and the nose will be held with both hands to avoid air leakage. Next, the technicians will instruct the participants to inhale or exhale and to avoid coughing or repetitive breathing throughout the exhalation or inhalation without interruption. The test will be conducted from 9 to 11 am to avoid the changes in individual lung function that occur throughout the day.

#### Primary outcome measurements

FVC, which refers to the maximum volume of gas exhaled after inhaling the maximal amount of gas possible, is the primary outcome indicator for this study [39]. It is an important indicator of the presence or absence of resistance in the airways. After breathing calmly, the subject will be requested to inhale to the total lung volume and quickly exhale all the air at once with maximum force. Each subject will repeat the exercise 3 to 8 times until three acceptable and reliable pulmonary function values are obtained. If such values are not obtained after 8 times, we will ask the subject to come for testing the next day so as to avoid inaccurate values due to excessive repetition. For FVC, the acceptable difference between the maximum and the second maximum is within 150 mL [40].

#### Secondary outcome measurements

Secondary outcome indicators in this study include FEV1, FEV1/FVC, MVV, and VC. FEV1 refers to the volume of gas exhaled by forced exhalation in 1 s after maximal inspiration; it is one of the most commonly used parameters to evaluate the degree of lung function damage [41]. The FEV1% predicted value is an important indicator of the degree of lung function impairment. For the FEV1 measurement, the subject will be asked to exhale rapidly within 1 s after maximum inspiration (total lung volume). As with FVC, the difference between the two FEV1 tests should be less than 150 mL.

FEV1/FVC is the most commonly used parameter to evaluate the presence of expiratory airflow obstruction. The Major Respiratory Society guidelines recommend the diagnosis of airflow obstruction when the ratio of FEV1 to FVC is less than a fixed threshold of 0.70 [42]. FEV1/FVC is negatively correlated with age, with lower FEV1/FVC values as age advances [43].

VC is the maximum volume that can be exhaled slowly and deeply after maximal inspiration and is also known as slow vital capacity. It is one of the most commonly used indices of lung capacity [44]. Subjects will be asked to exhale and inhale as deeply as possible evenly at a moderate speed and force. There must be no leakage or repetition of breaths during a cycle of exhalation and inhalation. The VC test is repeated a maximum of 5 times with a difference of less than 150 mL between the best and second-best values.

MVV is the ventilation volume obtained by repeating the maximum spontaneous breathing as fast and as deep as possible in a period of time and is a reliable index for the comprehensive evaluation of the pulmonary ventilation reserve [39, 45]. It is related to the strength of the respiratory muscles, the elasticity of the thorax and lung tissue, and airway resistance. Subjects will be asked to follow the physician’s instructions, after 4–5 normal breaths until the baseline expiratory volume is stable and to keep breathing at maximum respiratory amplitude and fastest respiratory rate for 12–15 s with a 3- to 5-min break between each of the three tests. There should be no air leakage during breathing, and the difference between the best two results should be < 8%.

### Statistical methods

The SPSS statistics software (IBM SPSS STATISTICS, 25.0 version, Armonk, NY) will be used for data analysis and statistical testing. The Kolmogorov-Smirnov test will be used to check whether the data conform to the normal distribution. The average ± standard deviation (SD) will be used to describe continuous variables, and categorical variables will be expressed as *n* (%). Paired sample *t*-test will be used for intra-group comparison, and one-way analysis of variance (ANOVA) and covariance analysis will be used for inter-group comparison. The homogeneity of variance will be tested before ANOVA followed by a comparison of between-group variability using the least significant difference method corrected for test level *α* using Bonferroni adjustment.

Covariance analysis will be used to control other non-interventional factors. Repeated measurement analysis of variance will be used to analyze the intervention effect at different intervention times. The statistical difference may be significant (if *P* < 0.05) and very significant (*P* < 0.01).

All missing data will be analyzed using intention-to-treat analysis. Multiple imputation will be used to fill missing completely at random and missing at random, and last-observation-carried-forward will be used to fill miss not at random data.

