## Methods

### Trial design

The prospective, parallel, single-blind, randomized controlled trial will evaluate the effects of different conditioning methods of TCHE on lung function in middle-aged and elderly people. It fulfills the requirements of the Standard Protocol Items: Recommendations for Interventional Trials (SPIRIT) checklist [23].

The subjects will be recruited from Mengcheng County, Anhui Province, China. A simple randomization will be used to divide them into a breath regulation group, body regulation group, heart regulation group, and control group in a 1:1:1:1 proportion. The subjects in the control group will receive health education only and maintain their previous lifestyle, and the three experimental groups will undergo exercise intervention (including warm-up, relaxation, and stretching) and health education for 6 months, 5 times a week, with each session lasting 60 min. The main and secondary results will be tested at baseline and at 3 and 6 months after the beginning of the intervention. An overview of the research program flow is presented in Fig. 1. The SPIRIT flow chart of the time points for enrolment, interventions, and assessments is shown in Fig. 2.

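### No primary model or visit is named for FVC and baseline FVC is not a stated covariate; the false-positive risk is about 7–10%, or up to about 16% if any listed between-arm test may count

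*Protocol article*

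**What the plan says.** All of this is in the protocol article.

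- **Primary outcome (Outcomes).** It is FVC. The section opens with "The changes of pulmonary function from baseline to the end of the interventions will be assessed", which points to change at the end of treatment but does not label it the primary time point. The Abstract describes changes at both follow-up visits.
- **Between-arm tests (Statistical methods).** "one-way analysis of variance (ANOVA) and covariance analysis will be used for inter-group comparison". Neither is given precedence.
- **Longitudinal test (same section).** "Repeated measurement analysis of variance will be used to analyze the intervention effect at different intervention times".
- **Covariates (same section).** "Covariance analysis will be used to control other non-interventional factors". Baseline FVC is not mentioned.
- **Within-arm tests (same section).** Paired t-tests "will be used for intra-group comparison".
- **Multiplicity (same section).** Pairwise arm comparisons after ANOVA use a Bonferroni-corrected level. Results are otherwise read at P<0.05, with P<0.01 called very significant.
- **Sizing (Sample size calculation).** One-way ANOVA with 80% power, alpha 0.05, SD 48, SD of the means 8.16 and 20% dropout gives 120 per group.
- **Visit timing.** Trial design says outcomes are "tested at baseline and at 3 and 6 months after the beginning of the intervention". Outcomes says "All results will be evaluated at baseline and 3 months and 6 months after the intervention by the same evaluator".

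**The concern.** For one primary variable, the text allows at least five between-arm tests: ANOVA at two visits, ANCOVA at two visits, and the group-by-time test. Nothing says which one answers the primary question. The Bonferroni step deals with the number of arm pairs, not with the choice of model or visit. If that choice can be made after the results are seen, the 5% level on which the trial was sized is not protected.

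There is a second cost. Baseline FVC is measured on everyone and usually predicts later FVC strongly. A plan that does not commit to adjusting for it may lose precision at no saving.

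The two descriptions of visit timing also matter. Read literally, the one in Outcomes would place the last test 6 months after training has ended.

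**Working it through.** **1. The plan's own sample size.** The effect size is f = 8.16/48 = 0.17, so f² = 0.0289. With four arms of n, the noncentrality is λ = 4n·f². At n = 96, λ = 384 × 0.0289 = 11.10 and the one-way ANOVA F test has power 0.803. At n = 95 the power is 0.799. Dropout of 20% gives 96/0.80 = 120. The stated figure is reproduced.

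**2. False-positive risk.** Trials were simulated under the null with 96 per arm, normal data and 10,000 runs per setting. The document gives no correlation between visits, so a common value ρ from 0.5 to 0.95 was assumed. The table shows the chance that at least one test in the set reaches P<0.05.

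| Tests that may count | Range over ρ |
|---|---|
| One prespecified ANCOVA at 6 months | 0.044–0.053 |
| ANOVA at 3 or 6 months (raw FVC) | 0.067–0.089 |
| ANCOVA at 3 or 6 months | 0.089–0.097 |
| ANOVA (raw FVC) or ANCOVA, 6 months only | 0.074–0.099 |
| ANOVA (raw FVC) and ANCOVA at both visits | 0.137–0.153 |
| The same four plus group-by-time (five tests) | 0.156–0.163 |
| Five tests, with ANOVA on change scores | 0.118–0.148 |

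Five independent tests would give 1 − 0.95⁵ = 0.226. That overstates the risk because these tests are correlated.

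The 6-month-only row uses raw FVC in the ANOVA. The raw-value and ANCOVA contrasts correlate at √(1−ρ²). The change-score and ANCOVA contrasts correlate at √((1+ρ)/2). Both equal 0.87 at ρ = 0.5. At ρ = 0.9 they are 0.44 and 0.97. So with change scores and ρ above 0.5, the inflation from this one choice should fall below the 0.074 end of the range. That case was not simulated separately.

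**3. Precision.** The ANCOVA residual variance is 1 − ρ² times that of raw follow-up values. Relative to change scores it is (1 − ρ²)/(2(1 − ρ)) = (1 + ρ)/2.

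| ρ (assumed) | Variance cut against raw FVC | Variance cut against change |
|---|---|---|
| 0.5 | 25% | 25% |
| 0.7 | 49% | 15% |
| 0.8 | 64% | 10% |
| 0.9 | 81% | 5% |

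The effect on power depends on what the SD of 48 describes, which the document does not say. If it is the SD of raw FVC, then at ρ = 0.7 λ becomes 11.10/0.51 = 21.76 and power rises from 0.803 to 0.983. If it is the SD of change, λ becomes 11.10/0.85 = 13.06 at ρ = 0.7 and power is 0.87. At ρ = 0.5, 0.8 and 0.9 the change-SD figures are 0.91, 0.85 and 0.83.

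**The case against.** The strongest reply is that the protocol narrows the choice more than it first appears. Outcomes speaks of change to the end of the intervention. The sample size rests on one-way ANOVA. Each procedure has a loose role, and the pairwise arm comparisons are corrected. A separate analysis plan may also settle the rest. Much of this stands, and it rules out several stronger readings:

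- **The error rate is three times nominal.** A reader might take this as a property of the plan. It needs a rule that any of the five tests may be claimed as success, with ANOVA on raw values, and the protocol states no such rule.
- **Most of the precision is thrown away.** This holds only if raw 6-month FVC is compared. The Abstract and Outcomes both describe changes, which already use baseline. Repeated-measures ANOVA that includes the baseline visit also uses it, and the ANCOVA may include baseline FVC although the text does not say so.
- **Adjustment will use variables measured after randomisation.** The Control group section records exercise and physical labour during the intervention period, but nothing lists them as covariates.
- **Arms will be ranked by their paired t-tests.** Between-arm comparison is assigned to ANOVA and ANCOVA, so this is not planned.
- **The sample size is wrong.** It is not. Sizing on an unadjusted test and then adjusting is conservative.

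The reply does not remove the core. The text itself prescribes two models for the same between-arm comparison and a third for the intervention effect over time, and it labels no visit primary. That goes beyond detail left for later.

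**Conclusion.** The point holds in a limited form. The protocol does not fix which model and visit decide the FVC question, and its multiplicity correction does not reach that choice. The false-positive risk is about 7–10% if only ANOVA (on raw FVC) versus ANCOVA at 6 months is open. It rises to about 16%, roughly three times nominal, if any of the five between-arm tests may count. One prespecified test gives 5%. These figures assume 96 evaluable per arm, normal data and equal correlations between visits of 0.5–0.95.

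The gain from committing to baseline FVC is 49–81% of residual variance against raw values and 15–5% against change scores, for assumed correlations of 0.7–0.9. The wording favours the smaller gain, but the document does not settle it.

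The visit timing is a plain inconsistency. The Abstract and Trial design count from the start of the intervention, and no follow-up after training is described. The phrase in Outcomes is therefore probably loose wording, but it concerns when the primary variable is measured and should be reconciled.

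**What to change.** In Statistical methods:

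- Name one primary analysis: FVC at 6 months after the beginning of the intervention, compared between the four arms by ANCOVA, or an equivalent mixed model, with baseline FVC as covariate.
- Limit all covariates to variables measured before randomisation.
- Keep the Bonferroni-adjusted pairwise arm comparisons, applied to this model.
- Label month 3, unadjusted ANOVA and repeated-measures ANOVA as supportive.
- Treat the within-arm paired t-tests as descriptive. A shift common to all arms, such as learning the test, can make them significant without any difference between arms.

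In Outcomes, reconcile the visit wording with the Abstract and Trial design. In Sample size calculation, state whether 48 is the SD of raw FVC or of change.

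The cost is wording only. Baseline FVC is already collected and the sample size stands. The change should be made before any outcome data are seen by arm.

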Traditional Chinese health exercise (TCHE) is an effective means of maintaining health and fitness and managing stress [17]. It regulates and enhances the functions of various parts of the human body through constant postural changes, breathing exercises, and mindfulness. It also presents characteristics of traditional Chinese medicine, including the application of meridians and acupoints and the regulation of qi, which increases its medical value [18]. TCHE plays important roles in the improvement and treatment of lung function, since these methods emphasize a close relationship between exercise and breathing. A number of studies have shown a significant improvement in the lung function of those who practice the TCHE [19–21]. Traditional lung rehabilitation therapy utilizes either physical or breathing exercise only. TCHEs combine these two types of exercise with mindfulness activities, which may have additional beneficial effects on lung function [22]. Different from and in contrast with traditional lung rehabilitation, which focuses on the rehabilitation treatment of patients after illness [15], TCHE focuses on disease prevention, a characteristic that reflects the preventive role of traditional Chinese medicine [18]. All TCHEs (such as Taijiquan, Baduanjin) include three types of regulation, namely “breath regulation,” “body regulation,” and “heart regulation,” all of which are indispensable and present in varying proportions across TCHE. Although previous studies have investigated the effects of TCHEs on lung function, no studies have explored the effects of each of these conditioning modalities on lung function separately. Therefore, depending on the modality of conditioning, the TCHEs will be divided into three exercise intervention groups: breath regulation group, body regulation group, and heart regulation group, in order to explore the magnitude of their effect on the improvement of lung function.

The purpose of this study is to analyze the effects of “breath regulation,” “body regulation,” and “heart regulation” on the improvement of lung function and to explore which modality is the most effective intervention for healthy middle-aged and older subjects.

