### Sample size calculation

Considering the results of a previous study that used forced vital capacity (FVC) as the primary outcome index [24], the sample size was calculated by one-way ANOVA in Power Analysis and Sample Size version 15.0.5 (PASS 15.0.5 NCSS, LLC, USA). With a power of 80%, an alpha of 0.05, a standard deviation of 48, a standard deviation of the means of 8.16, and a dropout rate of 20%, we aim to recruit a minimum of 120 subjects per each of the four groups.

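### If the Bonferroni correction covers all six pairs, the pairwise step is valid but needlessly conservative; a step-down rule would raise the chance of showing the best modality by about 3 to 10 points with the same data

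*Protocol article*

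**What the plan says.** The Statistical methods section sets out the between-group analysis of the four arms: a check of equal variances, a one-way ANOVA, and then a "comparison of between-group variability using the least significant difference method corrected for test level". The correction named there is Bonferroni. The section does not give the number of comparisons, and it does not say that the pairwise tests depend on a significant F test. No stepwise procedure is mentioned.

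The Background states the aim that these pairwise tests serve, which is to "explore which modality is the most effective intervention for healthy middle-aged and older subjects".

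The Sample size calculation section sizes the trial for the overall F test only: "the sample size was calculated by one-way ANOVA". The inputs listed there are "With a power of 80%, an alpha of 0.05, a standard deviation of 48, a standard deviation of the means of 8.16". One subject in five is expected to be lost, and the recruitment target per arm is at least 120.

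**The concern.** A significant four-arm F test says only that the means are not all equal. Which modality is best can be learned only from the modality-versus-modality pairs, so the rule for those pairs decides how often the trial can answer its own question.

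Single-step Bonferroni over six pairs protects against all six null hypotheses being true at once. With four means, however, the number of true pairwise nulls can only be 6 (all equal), 3 (three equal, one different), 2 (two equal pairs), 1 (one equal pair) or 0. Once any difference exists, at most three of the six can be true. Keeping the divisor at six after that point gives up power and gains no error control that is needed at the 5% limit.

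**Working it through.** **Inputs.** From the Sample size calculation section: α = 0.05, SD 48, SD of means 8.16, 20% dropout, 120 recruited per arm. From the Trial design section: four arms in 1:1:1:1. Assumed: all six pairs are tested, and the unadjusted ANOVA is used with normal data and equal variances.

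**Step 1: the plan's own figure.** With n per arm, λ = 4n(8.16/48)². At n = 96, λ = 4 × 96 × 0.0289 = 11.10 and the F test on 3 and 380 df has 80.3% power, so 80% is reached. Then 96/0.80 = 120 per arm. The stated sample size reproduces.

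**Step 2: critical values (380 df).** 0.05/6 gives t = 2.652; 0.05/3 gives t = 2.405.

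**Step 3: error bound under 0.05/6.** The bound is the number of true nulls × 0.05/6. Three equal arms: 3 × 0.00833 = 2.5%. Two equal pairs: 2 × 0.00833 = 1.67%. One equal pair: 0.83%.

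**Step 4: familywise error by simulation** (300,000 to 400,000 trials per pattern, 96 per arm, pooled variance).

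| True state | F test, then 0.05/6 | F test, then 0.05/3 |
|---|---|---|
| All four equal | 3.8% | 4.8% |
| Three equal, one different | 2.3% | 4.4% |
| Two equal pairs | 1.65% | 3.3% |

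The 0.05/6 rule without an F gate gives 4.1% when all arms are equal. Flat 0.05/3 without the gate gives 7.8% there, which is not acceptable. Shaffer's step-down without a gate stayed at or below 4.3% in every pattern run.

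**Step 5: patterns of means.** The protocol fixes the SD of the means but not their pattern. Scaling each pattern to 8.16:
- One modality above three equal arms by d: SD of means = d√3/4, so d = 8.16/0.433 = 18.8.
- Means 0:1:1:2 in units u, control lowest: SD = 0.707u, so u = 11.5 and the means are 0, 11.5, 11.5, 23.1.
- Equally spaced by u, control lowest: SD = 1.118u, so u = 7.3.

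The F test has about 80% power in all of them.

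**Step 6: chance that the best modality significantly beats both other modalities.**

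| Pattern | F test, then 0.05/6 | F test, then 0.05/3 | Gain (points) |
|---|---|---|---|
| One stands out, rest equal control | 36.2% | 46.6% | about 10 |
| 0:1:1:3 | 16.7% | 24.4% | 7.7 |
| 0:1:1:2 | 6.6% | 10.8% | 4.2 |
| Equally spaced | 3.9% | 6.8% | about 3 |

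Moving the control mean about in the first pattern raises the gain to at most about 10.7 points. For that pattern, Shaffer's step-down without any F gate gives 46.0% and Holm 40.8%.

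**The case against.** **The divisor of six is inferred.** If the sponsor meant only the three modality-versus-modality pairs, or only the three comparisons with control, Bonferroni is already 0.05/3 and nothing is lost. An article may leave this count to the full protocol or the analysis plan. This stands as a condition on the whole point. Six remains the natural reading of an LSD follow-up to a four-arm ANOVA.

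**The F gate is inferred too.** A reader might conclude that the plan pays twice for the same protection, once in the F test and again in the divisor. The text does not support that, because it never makes the pairwise tests conditional on F. The point does not need the gate: Shaffer's procedure works without one and rejects everything Bonferroni rejects.

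**The largest figures are easy to over-read.** A reader might take it that half of the 5% is always unused and that 10 points are always lost. With all arms equal, only about a quarter is unused. Ten points is close to the best case and needs the two other modalities to sit near control, whereas the Discussion expects all three to improve lung function. If they do, with means such as 0:1:1:2, the gain is about 4 points.

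**Bonferroni has a real advantage.** It has matching simultaneous intervals, and the Background also speaks of the magnitude of effects. This stands as the price of the change. If matching intervals are required, Tukey (multiplier 2.58 against 2.65) is the modest alternative.

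**There are two follow-up visits.** If the pairwise rule were applied to FVC at both 3 and 6 months, then with an assumed between-visit correlation of 0.5 to 0.9 and three equal arms, the overall error would be 3.4 to 4.3% under 0.05/6 but 6.4 to 8.1% under 0.05/3. The fix is therefore limited to one primary time point. The Outcomes section's reference to change up to the end of the interventions suggests a single one, but does not settle it.

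**Conclusion.** The point holds as an efficiency gain, on condition that Bonferroni is meant over all six pairs. The planned rule is valid. It should not be read as a breach of error control, since it errs on the cautious side.

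Its cost at the planning values (96 completers per arm, SD 48, SD of means 8.16) is about 3 to 10 points in the chance that the best modality beats both others. With all 120 per arm contributing fully, the one-stands-out pattern gives 50.1% against 60.6%, a gain of the same size.

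Nor should the low pairwise power be blamed mainly on Bonferroni. At 96 per arm the chance is still below 50% after the change in the patterns tabulated, because the trial is sized for the F test alone. The better rule reduces that shortfall but does not remove it.

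**What to change.** For FVC at the single primary time point, replace single-step Bonferroni by wording such as: *The six pairwise p-values are ordered from smallest to largest and compared in turn with 0.05 divided by 6, 3, 3, 3, 2 and 1 (Shaffer's step-down); testing stops at the first that is not significant.* This needs no F gate, never rejects less than Bonferroni and keeps the familywise error at or below 5%.

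Alternatively, state that pairwise tests are done only if the four-arm F test is significant at 0.05, and then test each pair at 0.05/3 = 0.0167. The flat 0.05/3 must not be used without that written gate.

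Either way, state the number of comparisons and the time point. Show Tukey or Bonferroni simultaneous intervals for estimation, with a note that they may occasionally include zero for a contrast declared significant.

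The cost is one sentence of analysis wording, no new data and the loss of exactly matching intervals. The Trial status section puts the start of recruitment after the protocol was written, so the rule could be set before any outcome data were seen.
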